### Data collection

#### Level of the patients and relatives or close personal contacts

At the level of the patients and their relatives or close personal contacts primary and secondary data are collected and analysed.

The primary data of the patients enrolled in the study and of their relatives or close personal contacts are collected by practice employees who are trained for this task (control networks) and case managers (intervention networks) by means of the assessments created for this purpose (baseline and follow-ups). The primary data is recorded in the data management system CentraXX (Kairos GmbH, Bochum) at the Institute for Community Medicine, University Medicine Greifswald using the eCRFs (electronic case report forms) completed based on the assessments.

Within the framework of the process evaluation, the study also investigates the acceptance of the intervention. Focusing on the perspective of patients and their relatives and close personal contacts, as well as its feasibility and implementation, it is evaluated by means of case analyses, focus group meetings or expert interviews. Appropriate instruments have been developed for this purpose.

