**Methods:**

The project is designed as a prospective controlled study and compares geriatric patients from practice networks in different regions in Germany. Inclusion criteria are: Age ≥ 70 years and care requirements from two different care complexes (identified with the screening instrument ‘Angelina’-questionnaire). The intervention is the use of a geriatric case management, where health care is organised based on patient-specific care requirements. Five practice networks of physicians will implement the intervention (*n* = 3200 patients) and three practice networks will serve as the control group (*n* = 1200 patients). The primary endpoint is the ability to manage activities of daily living, measured using the Barthel Index. The patients in the intervention group receive geriatric case management and the patients in the control networks receive standard care (“care as usual”). The analysis of the primary data, which is pseudonymised, occurs according to the intention-to-treat principle. For this purpose, the endpoints will be analysed using a group comparison after 12 months. For the health economic analysis, secondary data from the statutory health insurance providers will be included in the analysis, in addition to the primary data. Data for the analysis of the effects the concept has on the GP practices as well as on the satisfaction of the project participants will be collected with questionnaires and interviews with experts.

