## Methods/ design

### Study design and procedure

The RubiN project is to be conducted as a prospective controlled intervention study in a clinical setting. Five practice networks, which are certified according to § 87b SGB V implement regionally adapted assessment-based case management. This certification of the practice networks provides a verification of special management skills [11]. The patients of the GP practices in these practice networks make up the intervention group. There are 640 patients per network, thus 3200 patients in total. Three further practice networks conduct the care of the patients as usual, without implementing case management. The patients of the GP practices in these three practice networks form the control group. It is comprised of 400 patients per network, thus 1200 patients in total (see Sample size calculation).

All patients receive the baseline assessment (BL) (see Table 1). In the intervention networks the patients included in the study then receive geriatric case management, designed according to patient-specific care requirements, for a period of 12 months. The patients in the control networks receive “care as usual”.

**Table 1 Tab1:** Outcome parameters for the levels (patients and relatives and close personal contacts)

Outcome	Measurement instrument/ operationalisation	Data collection point

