### Intervention

Health care professionals (qualified nurses, therapists or health care assistants (HCA)) receive the multiprofessional geriatric care training “GeriNurse” [13]. This is a 210-h training course (online and practical) and contains the following topics: health and project management, risk identification (preparation of clinical pathways), case management, risk management, accounting procedures, controlling, care management (regional neighbourhood management, public health, committee work).

Four case managers per practice network will receive the qualification, thus 20 in total for the RubiN project.

Based on the results of the patient’s baseline assessment the trained case managers perform a risk assessment. Based on the identified care requirements, patients are categorised as mild, moderate or severe cases. This provides the structure to determine the workload for the case managers in each case for the following 12 months (see Table 2) and a patient-specific, optimal treatment and/or care plan for the geriatric patient is prepared. The case managers monitor developments and progressions on a case-by-case basis, i.e. they make assessments and determine whether the care plan is to be followed or if it needs to be corrected or adjusted. The case managers identify care gaps and if required assess the care situation of these patients by means of case discussions and “round table” conferences. In doing so, they work closely with the GP and coordinate the care of the geriatric patients by being active across sectors and working with all other health professions in their respective practice network.

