### Follow-up assessments

After 12 months, the 12-month follow-up assessment (FU12) takes place both in the intervention group and the control group. It uses the same measurement instruments as the baseline assessment. After a further 9 months, this is followed by the 21-month follow-up assessment (FU21) for the patients who reach this point within the duration of the project. Aside from the personal data of the patient only data related to the primary endpoint, the Barthel Index, is collected again.

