### Limitations

This project constitutes a regional comparison. This is statistically not as robust as a grouping by randomisation at the patient level (RCT). An RCT was not possible here as the intervention is implemented as a regional structure.

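### Barthel assessor type is fully aligned with arm, and nothing in the article stops a case manager from scoring the result of their own work at follow-up

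*Protocol article*

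**What the plan says.** The abstract (Methods) fixes the endpoint: "The primary endpoint is the ability to manage activities of daily living, measured using the Barthel Index". Table 1 schedules it at baseline, FU12 and FU21, and Follow-up assessments says of FU12: "It uses the same measurement instruments as the baseline assessment".

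Data collection (level of the patients and relatives) says that the primary data "are collected by practice employees who are trained for this task (control networks) and case managers (intervention networks"). The same sentence covers the baseline as well as the later assessments, so the split by arm holds at every time point.

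Under Intervention, "the trained case managers perform a risk assessment" from the baseline results. This puts patients into a mild, moderate or severe category and sets the case manager's workload for the next 12 months. The section adds: "The case managers monitor developments and progressions on a case-by-case basis". There are four case managers per intervention network. In the control arm there are none: "Three further practice networks conduct the care of the patients as usual, without implementing case management" (Study design and procedure).

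Limitations opens with "This project constitutes a regional comparison" and discusses only the absence of patient-level randomisation. It does not mention who assesses the outcome.

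**The concern.** Assessor type and treatment coincide in all eight networks. No network mixes the two staff categories, so a model that adjusts for differences between providers and between networks (Data analysis, patient level) has no contrast from which to estimate an assessor effect separately from the treatment effect.

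The two staff categories also differ in their stake. At FU12 a case manager may be recording the result of their own 12 months of work. Their baseline assessment also serves care planning, a purpose it does not have for control staff. If scoring drifts with that role during follow-up, the drift enters the 12-month Barthel difference and a larger sample does not reduce it. The article hopes the results will support widespread implementation, so the primary comparison should be protected where this can be done cheaply.

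**Working it through.** **1. The plan's own figure.** Inputs from Sample size calculation: alpha 5% (two-sided reproduces the figure), power 85%, d = 0.3, ratio 3:1, ICC 0.15, dropout 33%. The two-sided t-test calculation gives 533.98, i.e. 534, as stated; the normal approximation gives 134 + 402 = 536. Then 534 × 5.5 = 2937, and 2937/0.67 = 4384. The plan reproduces.

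**2. Planned precision.** SE = 0.3/(1.960 + 1.036) = 0.100 SD. As a cross-check from the planned numbers after dropout and design effect: 3200 × 0.67/5.5 = 390 and 1200 × 0.67/5.5 = 146, so SE = √(1/390 + 1/146) = 0.097 SD.

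**3. Follow-up-only shift, unadjusted comparison.** Let b be a systematic scoring difference between arms at FU12, in SD, with no true effect. The chance of a significant result is Φ(b/SE − 1.96) + Φ(−b/SE − 1.96). The documents give no value for b; the range is assumed.

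| b (SD) | SE 0.100 | SE 0.097 |
|---|---|---|
| 0.05 | 8% | 8% |
| 0.10 | 17% | 18% |
| 0.15 | 32% | 34% |
| 0.20 | 52% | 54% |

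A shift of 0.10 SD is one third of the target d = 0.3.

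**4. Constant offset, baseline-adjusted comparison.** If the same offset b is present at baseline and FU12, adjustment leaves b(1 − ρ), with SE 0.100 × √(1 − ρ²). Here ρ is the baseline–follow-up correlation, assumed to be 0.5 to 0.8, and the SE is taken to shrink equally at all levels.
- b = 0.10, ρ = 0.5: remainder 0.05, SE 0.087, false positives 9%.
- b = 0.10, ρ = 0.8: remainder 0.02, SE 0.060, false positives 6%.
- b = 0.20: 21% (ρ = 0.5) and 10% (ρ = 0.8).

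**5. Follow-up-only shift, baseline-adjusted comparison.** The whole of b remains and the SE is smaller. For b = 0.10: 0.10/0.087 = 1.15 gives 21%, and 0.10/0.060 = 1.67 gives 38%. Baseline adjustment does not protect against this component.

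**6. Changing staff category at follow-up only.** Suppose case managers assess at baseline and practice employees at FU12 in the intervention arm. An offset b is then present only at baseline, and adjustment turns it into a bias of size ρb. For b = 0.10: 0.05/0.087 gives 9%, and 0.08/0.060 = 1.33 gives 27%. Across the assumed range this is no better than step 4, and at ρ = 0.8 it is much worse (27% against 6%).

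**The case against.** The strongest reply is that the design is symmetric over time. Each arm uses the same staff category at baseline and at follow-up, so a constant difference in scoring habits is already in the baseline and shrinks under adjustment (step 4). The article plans multivariate and multilevel models, and the choice of covariates belongs to an analysis plan that is not shown. This stands, and it limits the concern to shifts that arise between baseline and follow-up.

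A reader might infer that each patient is assessed at follow-up by their own case manager, or that the same person does the baseline, sets the severity category and scores FU12. The article does not say so. With four case managers per network, a swap is compatible with the text, and rostering is a detail an article may leave to the full protocol. What stands is that the article, which does fix the assessor category by arm, does not exclude it.

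A reader might also infer that any scoring difference adds in full to the treatment effect, or that no positive result could be attributed to case management. The first is true only of a follow-up-only shift or an unadjusted comparison. The second goes too far: the insurer claims data on costs and avoidable hospitalisations do not depend on these assessors, although they are not the primary endpoint.

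Finally, the article says that data are collected, not how the Barthel Index is scored, nor which instruments patients complete themselves. Neither the size nor the direction of any bias can be derived from it.

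**Conclusion.** The concern holds in a limited form. Staff category is fully aligned with arm for the primary endpoint, the assessors are unblinded by role, those in the intervention arm belong to the group that delivers the intervention, and Limitations does not mention it. The planned adjustment for providers and networks cannot separate assessor from treatment.

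The size depends on which kind of bias is present. An assumed 0.10 SD offset that is constant over time gives about 6–9% false positives after baseline adjustment. The same shift arising only during follow-up gives about 17% unadjusted, and 0.20 SD about 52%. These figures rest on assumed shifts, an assumed correlation of 0.5 to 0.8 and the plan's own precision. They show how sensitive the comparison is; they do not estimate a bias that has occurred.

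**What to change.** 1. In Data collection, state that FU12 and FU21 in the intervention networks are done by a case manager of the same network who has not managed that patient.
2. Keep the staff category the same at baseline and follow-up within each arm. Do not move to another category at follow-up only (step 6). This matters because registration was retrospective, so some baselines may already have been taken.
3. Make the primary Barthel comparison baseline-adjusted.
4. In Limitations, name the remaining unblinded, arm-specific assessment. The swap removes the scoring of one's own work. It does not remove the difference in staff category, and the swapped assessors are still unblinded members of the intervention team.

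Cost: protocol wording, rostering and some travel, with no extra staff and no extra assessments.

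Optional: using trained practice employees at both baseline and follow-up in the intervention arm would remove the difference in assessor type. It means training staff in about 22 × 5 = 110 practices for up to 3200 patients. Those employees would still be unblinded.

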#### The level of the practices and networks of physicians

At the level of the practices and networks of physicians, surveys and process analyses will also be conducted.

In order to conduct the process evaluation, alongside the quantitative and administrative data from patients, relatives and close personal contacts, medical and non-medical service providers, additional data and information will be generated by means of guided expert interviews and the formation of interprofessional focus groups.

For the evaluation of the special features of practice networks with regard to the course of the health care provision in terms of interprofessional cooperation and the special role of case management in this scenario a special interview technique will be employed: the Pictor technique [15, 16].

### Health economics

The health economic assessment focuses on two research objectives: 1) The project’s impact on overcoming the sectoral divide as experienced by health providers and patients. 2) The project’s economic impact measured as the cost per reduction in ambulatory sensitive hospital cases (ACSC), which is interpreted as a quality indicator for ambulatory services [17].

The health economic analysis includes quantitative and qualitative components using primary patient and service provider information and the secondary data from statutory health insurances. Cost include all relevant claims experienced by the health insurances, e.g. of outpatient, inpatient and emergency treatments, of medicinal products, remedies, aids and rehabilitation (if these are paid for by the health insurance provider).

ACSC are measured as the difference in the average frequency in the intervention and control groups.

The analysis of the sectoral gaps uses qualitative methods. Based on semi-structured expert interviews with medical and non-medical professions across the different practice networks, information is gained about experiences with sectoral barriers in the provision of care.

The goal is to highlight how the RubiN care concept can contribute towards solving the issues identified in relation to interfaces in health care provision.

### Ethics and data protection

All of the recruitment and data collection procedures within the framework of the study occur on the basis of the ethical principles for medical research involving human subjects (The Declaration of Helsinki) as well as the recommendations for safeguarding good scientific practice of the German Research Foundation (DFG), the Guidelines and recommendations for ensuring Good Epidemiological Practice (GEP) [18], the principles of the “Good Practice in Secondary Data Analysis” [19], the Memorandum III “Methods for Health Services Research” [20] and also the standards of the German Evaluation Society (DeGEval) [21].

There is a harmonised data protection concept for the RubiN project for all partners in the consortium.

The project has received the approval of the Ethics Committee of the University of Greifswald (BB188/18), issued 17.01.2019.

### Data analysis

#### Patient level

To test the structural equality of the intervention and control groups the characteristics of the patients and the GP practices at the point in time t_0_ (baseline) are examined using descriptive and analytical statistical procedures (group comparisons).

The primary analysis of results follows the intention-to-treat principle and includes all the patients involved in the study. After the follow-up (t_1_, 12 months) the patients from the intervention and control group are analysed with regard to the different outcomes in a group comparison. The evaluation is performed with multivariate models and multilevel analyses, in order to be able to adjust for possible differences between the service providers and between the practice networks. The analyses are conducted using the statistics software SAS 9.4.

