### Sample size calculation

The number of cases was estimated for the primary endpoint (Barthel Index) of the RubiN project. The following parameter assumptions were made:
Error 1st type (α): 5%.Error 2nd type (β): 15% (≙ power of 85%)Effect size (d): 0.3Intervention/control ratio (on the patient level): 3/1Assumed intracluster correlation coefficient: 0.15Assumed drop-out rate: 33%

To demonstrate an effect of d = 0.3 with the mentioned assumptions, *n* = 534 participants are needed (400 in the intervention group and 134 in the control group). It is estimated that about 22 practices will participate in each practice network, each of which will be able to recruit an average of 30 participants. With an assumed intracluster correlation coefficient [14] of 0.15, a “design effect” of 5.5 for the regional design must be taken into account in the sample size planning. This increases the necessary sample size to *n* = 2937.

With an assumed dropout rate of 33%, 4384 (2937/0.67 = 4384) participants should be included, rounded up to 4400. The 5 intervention networks will each recruit about 640 participants (3200), the 3 control networks will each recruit about 400 participants (1200) (ratio 2.7:1, rounded up 3:1).

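### Each practice network lies wholly in one arm, so the planned adjustment between networks cannot be a fixed-covariate adjustment; the model form and small-sample degrees of freedom must be fixed to hold the 5% alpha if networks differ.

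*Protocol article*

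**What the plan says.** **Allocation.** Under Study design and procedure, five networks implement case management. For the others, "Three further practice networks conduct the care of the patients as usual, without implementing case management", and "The patients of the GP practices in these three practice networks form the control group". Every network therefore belongs to one arm only.

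**Analysis.** Under Data analysis, Patient level, the outcomes are to be compared in multivariate and multilevel models. The stated purpose of these models is: "in order to be able to adjust for possible differences between the service providers and between the practice networks". Nothing there says whether network is a fixed or a random term, or what reference distribution applies to the treatment effect.

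**Sample size.** The stated error rate is "Error 1st type (α): 5" percent, with 85% power, d = 0.3, one ICC of 0.15 and 33% dropout. The clustering input is "about 22 practices will participate in each practice network, each of which will be able to recruit an average of 30 participants". The resulting design effect of 5.5 is described as one "for the regional design must be taken into account in the sample size planning", although it is built from practice size. Recruitment is then set out by network: "The 5 intervention networks will each recruit about 640 participants (3200), the 3 control networks will each recruit about 400 participants (1200").

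**Limitations.** The article concedes that a regional comparison is statistically weaker than patient-level randomisation. It does not say that only eight networks carry the comparison.

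**The concern.** Adjusting for differences between networks suggests that such differences can be taken out of the treatment comparison. That is possible only when both treatments occur within a network, and here they never do. Three readings of the sentence lead to three different analyses:

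- Network as a fixed effect: the treatment effect cannot be estimated.
- Practice as the only random level: practices within a network are treated as independent, and any network variance is left out of the standard error.
- Network as a random effect: the standard error can be right, but the contrast rests on 8 − 2 = 6 degrees of freedom, so a normal or large-sample reference is too lenient.

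The standard error and p-value of the primary Barthel Index result depend on which reading is followed. None of the three removes a systematic difference between the intervention regions and the control regions.

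**Working it through.** **1. Reproducing the plan's own figure.** A two-sided 5% t-test with 85% power, d = 0.3 and 3:1 allocation needs 133.5 + 400.5 = 534 patients, as stated. A one-sided test would need 428 (normal approximation), so the plan is two-sided. Then 534 × 5.5 = 2937, and 2937/0.67 = 4384. The usual design effect is 1 + (30 − 1) × 0.15 = 5.35, and 5.5 equals 1 + 30 × 0.15. Either way the cluster is a practice of about 30 patients, with no network component.

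**2. Aliasing.** Take one row per network and columns for the intercept, arm and seven network indicators. That gives 9 columns of rank 8. The intercept and network indicators alone also have rank 8. Arm adds nothing, so its effect is not estimable beside fixed network effects.

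**3. Practice-only error term.** Inputs from the article: 5 networks of 640 and 3 of 400, 67% retained (428.8 and 268 evaluable per network), total ICC 0.15. With total variance 1, the residual variance is 0.85. The network ICC, ρ, is **assumed**, and the practice component is 0.15 − ρ. At 30 recruits per practice there are 640/30 = 21.33 practices per intervention network and 400/30 = 13.33 per control network, about 147 in all.

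- Variance the practice-only model would report: V0 = (0.85/428.8 + 0.15/21.33)/5 + (0.85/268 + 0.15/13.33)/3 = 0.00661, so SE0 = 0.0813.
- True variance: V = ρ(1/5 + 1/3) + (0.85/428.8 + (0.15 − ρ)/21.33)/5 + (0.85/268 + (0.15 − ρ)/13.33)/3.
- Type I error = 2 × (1 − Φ(1.96 × SE0/SE)).

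At ρ = 0.01, V = 0.0116, SE = 0.1077, SE0/SE = 0.755, and the error is 2 × (1 − Φ(1.480)) = 13.9%.

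The article also gives about 22 practices in every network. That does not fit 400 recruits per control network at 30 each (22 × 30 = 660). Taking 22 practices per network (176 in all) gives SE0 = 0.0713. Both readings are shown:

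| Assumed network ICC | SE, about 147 practices | Type I error | SE, 176 practices | Type I error |
|---|---|---|---|---|
| 0 | 0.0813 | 5.0% | 0.0713 | 5.0% |
| 0.005 | 0.0954 | 9.5% | 0.0874 | 11.0% |
| 0.01 | 0.1077 | 13.9% | 0.1009 | 16.6% |
| 0.02 | 0.1288 | 21.6% | 0.1236 | 25.8% |
| 0.05 | 0.1776 | 37.0% | 0.1748 | 42.4% |

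A simulation of 20,000 runs on the first reading gave 9.8%, 14.0%, 21.4% and 37.8% for ICC 0.005 to 0.05, in line with the formula.

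**4. Network error term, reference distribution.** P(|t6| > 1.96) = 9.8%, against 5% at the correct cut-off of 2.447. Simulating a mixed model with a REML network variance gave 8.0%, 9.1% and 9.6% with 1.96, and 3.3%, 4.4% and 4.8% with t on 6 df, at ICC 0.01, 0.02 and 0.05. A cruder comparison of unweighted network means with pooled variance ran higher, up to about 12% with 1.96 and 6.5% with t on 6 df as the network ICC approached 0, because the control networks are smaller. The Welch form stayed between 4.5% and 5.3%.

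**The case against.** The strongest reply is that the sentence names multilevel analyses and lists both service providers and networks as sources of difference. Its natural reading is a model with practice and network levels, which is close to the remedy asked for here. Nothing says that network will be a fixed covariate, that it will be dropped, or that a normal reference will be used. This is also a condensed article, and degrees-of-freedom methods commonly sit in a full protocol or SAP that is not shown.

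Most of that stands. A reader might infer that the plan omits network variance, or that its type I error far exceeds 5% as a matter of fact. The documents support neither: a random network term is compatible with the text, and without a network-level ICC the error could be as low as 5%. A flat statement that false benefit would be declared several times too often is also unsupported, because the inflation depends on both the model and the assumed ICC. The limitations section partly concedes the weakness of a regional comparison.

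What the reply does not answer is the nesting. The article states an aim, adjustment between networks, that this allocation cannot meet in the ordinary sense. The only place where it quantifies clustering stops at the practice while calling the result regional. The plan itself expects that networks may differ, so zero network variance is not its own premise.

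**Conclusion.** The point holds in conditional form. It is certain from the document that network is nested in arm, that a fixed network term is aliased with treatment, that 6 degrees of freedom carry the contrast, and that the sample size has no network component. A random network term makes the interval honest about regional variation but leaves regional confounding in place.

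The size rests on an assumed network ICC and on a model that the wording permits but does not state. With a practice-only error term, type I error is unharmed at ICC 0, roughly doubles at 0.005, and is about three times the nominal 5% or more from 0.01 upward on either reading of the practice count. If a random network term is used, which fits the text best, the inflation is less than twofold in the mixed-model simulation and arises only with a normal or large-sample reference.

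**What to change.** In Data analysis, Patient level, state that:

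- the primary model has patients within practices within networks, with random practice and random network-within-arm intercepts;
- network is never a fixed effect;
- the treatment effect is tested with small-sample degrees of freedom (Kenward-Roger, or t on about 6 df);
- an analysis of the eight network means is reported as a check, in a form that allows for unequal network sizes.

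In Limitations, add that regional confounding remains after this modelling and that only eight networks carry the contrast.

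This costs some analysis wording and a few lines of SAS code, with no change to recruitment or data collection. The price is wider confidence intervals. On the inputs above (about 147 practices, 6 df), power for d = 0.3 is 86% at network ICC 0, 75% at 0.005, 64% at 0.01 and 50% at 0.02. That loss comes from the design; the model only makes it visible.
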